##### Sample Size Considerations

The study will be adequately powered to detect a clinically important 20% absolute difference in the primary outcome between each intervention arm and usual care and similar 20% difference between the 2 intervention arms (20% has been previously identified by a consensus of Canadian experts as the required minimum clinically important difference for any new hypertension [or any other cardiometabolic] intervention directed at patients with diabetes [53]). Based on pilot data collected in 60 seniors residing in supportive living at two Edmonton sites, only 18% were within the therapeutic range at baseline. Assuming 5% improvement with usual care (related to secular or temporal trends and trial participation or Hawthorne type effects), 20% further improvement with telemonitoring, and a further 20% improvement with telemonitoring + case management, a 2-tailed alpha of 0.05, power of 0.80, the required sample size will be ~80 patients per arm or 240 total. Accounting for ≈20% attrition over 1 year, 100 patients per arm or 300 patients total will be recruited.

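### About 80 evaluable patients per arm gives roughly 77% and 72% power for the two 20-point contrasts, not the stated 80%

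*Protocol article*

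**What the plan says.** The inputs, the result and the power claim all stand in one paragraph of the protocol article (Aim 1, Sample Size Considerations).

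- **Target.** A "clinically important 20% absolute difference in the primary outcome between each intervention arm and usual care", and a "similar 20% difference between the 2 intervention arms".
- **Starting point.** In pilot data from 60 seniors, "only 18% were within the therapeutic range at baseline".
- **Assumed gains at one year.** "Assuming 5% improvement with usual care", then "20% further improvement with telemonitoring", then "a further 20% improvement with telemonitoring + case management".
- **Result.** With "a 2-tailed alpha of 0.05, power of 0.80, the required sample size will be ~80 patients per arm or 240 total", raised to 100 per arm (300 in total) for roughly 20% attrition.

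The Data Analysis section under the same aim names chi-square tests for dichotomous outcomes. It applies them to each intervention arm against control and then to the two intervention arms against each other.

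**The concern.** A 20-point difference does not need the same number of patients at every base rate, because the binomial variance grows as the proportions approach 50%. The plan's assumptions place the two 20-point contrasts at 23% versus 43% and at 43% versus 63%. Both lie closer to 50% than a contrast that starts from the 18% baseline. A single figure of about 80 per arm for both is therefore suspect, and it looks like the answer for a lower base rate.

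The contrast with the highest variance is telemonitoring plus case management against telemonitoring alone. It is the only one that shows what case management adds, and the paragraph names it as powered for the difference that it calls the minimum clinically important one. A null result there would be read against a claimed 20% risk of missing a true 20-point effect, when the design carries a higher risk.

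**Working it through.** **Inputs** (Sample Size Considerations unless noted)

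- Two-sided alpha 0.05, so z = 1.960. Power 0.80, so z = 0.8416. Allocation is 1:1:1 (Study Design).
- One-year proportions: usual care 18% + 5% = 23%; telemonitoring 23% + 20% = 43%; telemonitoring plus case management 43% + 20% = 63%.
- Attrition 20%. Test: chi-square (Data Analysis).

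**Formula** (pooled variance under the null, p̄ the mean of the two proportions)

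n per arm = [1.960·√(2p̄(1−p̄)) + 0.8416·√(p₁(1−p₁) + p₂(1−p₂))]² / (p₂−p₁)²

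**Step 1: find what gives about 80**

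- 18% versus 38%: p̄ = 0.28. (1.960·√0.4032 + 0.8416·√0.3832)² / 0.04 = (1.2445 + 0.5210)² / 0.04 = 77.9, so 78 per arm.
- If the 5% is read as a relative gain, usual care is 18% × 1.05 = 18.9%, and 18.9% versus 38.9% gives 79.4, so 80 per arm.

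Either pair is compatible with the stated figure. Neither is the pair obtained by adding 5 points to 18%.

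**Step 2: apply the formula to the plan's own proportions**

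- 23% versus 43%: p̄ = 0.33. (1.960·√0.4422 + 0.8416·√0.4222)² / 0.04 = (1.3033 + 0.5469)² / 0.04 = 85.6, so **86 per arm**.
- 43% versus 63%: p̄ = 0.53. (1.960·√0.4982 + 0.8416·√0.4782)² / 0.04 = (1.3834 + 0.5820)² / 0.04 = 96.6, so **97 per arm**.

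**Step 3: power with 80 evaluable per arm**

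Power = Φ{[(p₂−p₁)·√80 − 1.960·√(2p̄(1−p̄))] / √(p₁(1−p₁) + p₂(1−p₂))}

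| Contrast | Needed per arm | Power at 80 | Exact power at 80 (Pearson chi-square) | Power at 100 (no attrition) |
|---|---|---|---|---|
| 23% vs 43% | 86 | Φ(0.747) = 77% | 78% | 86% |
| 43% vs 63% | 97 | Φ(0.586) = 72% | 72% | 81% |
| 23% vs 63% | 23 | >99% | >99% | >99% |

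**Step 4: try other formulas**

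| Method (two-sided) | 23% vs 43% | 43% vs 63% |
|---|---|---|
| Pooled | 86 | 97 |
| Unpooled | 83 | 94 |
| Arcsine | 85 | 97 |
| Continuity-corrected | 96 | 107 |

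No two-sided version gives 80 for either contrast. One-sided versions give 68 and 76, or 77 and 86 with continuity correction, but they contradict the stated two-tailed alpha.

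**Step 5: detectable difference and attrition**

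- Solving the power formula for 80% at n = 80 gives 20.7 points from a base of 23% and 21.9 points from a base of 43%.
- The attrition step itself is correct: 80 / 0.80 = 100. Applied to the recomputed figures, it gives 86 / 0.80 = 107.5, so 108 per arm, and 97 / 0.80 = 121.25, so 122 per arm (366 in total).

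**The case against.** **The first contrast is close to rounding.** The paragraph writes its result as approximate. The unpooled formula needs only 83 for 23% versus 43%, power at 80 is 77–78%, and the detectable difference is 20.7 points against a target of 20. This is fair: taken alone, this contrast would be a minor point. It does not help the other one, where 94 to 97 are needed and power is about 72%.

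**The derivation of the 80 is unknown.** The document calls the 20% absolute but does not label the 5%, and the relative reading fits the stated figure slightly better than ignoring the gain does. So it cannot be said with confidence that a step was left out. The conclusion does not depend on this. On the relative reading the next contrast is 38.9% versus 58.9%, which still needs 97 per arm and has 72% power at 80.

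**One hundred are recruited, and adjustment may help.** With no attrition, power would be 86% and 81%. The first contrast reaches 80% if attrition stays at or below about 14% (86 of 100 retained); the second tolerates only about 3% (97 of 100). The plan itself assumes about 20%. The Data Analysis section also foresees logistic models adjusting for age, sex, SBP and residential site, which could recover some power. The document gives no baseline correlation from which to quantify that, and it lists the chi-square comparison first. The possible gain bears on how the figure is restated, but it does not support the figure as written.

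**Conclusion.** The concern holds. On the plan's own proportions, about 80 evaluable patients per arm does not deliver the stated 80% power for either 20-point contrast. The shortfall is small for telemonitoring versus usual care (about 77%). It is material for case management versus telemonitoring alone (about 72%, so a 28% rather than a 20% chance of missing a true 20-point effect). Case management versus usual care is amply powered.

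This rests on adding the gains as absolute points, an unadjusted chi-square test at two-sided 0.05 for each contrast, and the planned 20% attrition. If the 5% is read as relative, the first contrast reaches 80% and the between-intervention contrast stays at 72%.

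**What to change.** Keep 300 patients and correct the paragraph:

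- State the assumed one-year proportions outright (23%, 43%, 63%), so that the reading of the 5% is no longer open.
- State that 100 per arm with 20% attrition leaves 80 evaluable, which gives about 77% power for 43% versus 23% and about 72% for 63% versus 43% by unadjusted chi-square. Alternatively, give the differences detectable with 80% power: about 21 and 22 points.
- Remove the claim of 80% power for the between-intervention contrast, unless power is re-derived for a baseline-adjusted primary analysis with its assumed correlation stated.

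The cost is wording only: two stated power figures become less favourable, and recruitment, outcome and tests do not change. If the sponsor prefers to deliver 80% power for both 20-point contrasts with the unadjusted test, the cost is 122 per arm, or 366 − 300 = 66 more patients.

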#### Aim 2: Usability and Acceptability of Telemonitoring

Assessment of usability and acceptability is critical for all technology-enhanced care interventions because unanticipated and undesired effects can commonly occur after implementation [54-56]. End-user input into system design and operation is needed throughout the evaluation process; otherwise, interventions risk being ineffective, unusable, or unsafe [54,55]. Usability testing involves assessment of the human-computer interaction and, specifically, issues related to use, interface, design, and function are examined [57,58]. System evaluation is performed iteratively and includes assessment then redesign and retesting.

Usability and acceptability testing (device, data transmission, health portal) will be performed using well-accepted frameworks [57,59-61]. The evaluation will focus on functional goals (features, format, and interface), usability needs (outcome impact goals, end users’ requirements, and information needs), and end-users’ perceptions of the facilitators and barriers to use. End users that will be considered will include random samples of seniors with hypertension, family members who are primary caregivers, pharmacist case managers, and primary care physicians. We will perform usability and acceptability testing of the refined telemonitoring intervention at the beginning of the study and during the study. The evaluation will use standard mixed methods approach, with focus groups of all stakeholders, semistructured indepth interviews with think aloud and talk back with patients, and repeated surveys regarding the technology itself [54,55,57,58,60,62,63].

#### Aim 3: Cost-Effectiveness of Telemonitoring ± Case Management

##### Outcomes

The total and incremental cost for each intervention compared to usual care will be calculated (Table 2 and Figure 3), and the cost per decrement in SBP (cost-effectiveness model A), and incremental cost/QALY gained (cost-utility model B), will be determined.

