**Results:**

Outcomes will be ascertained at 6 and 12 months. Within-study-arm change scores will be calculated and compared between study arms. These include: (1) clinical outcomes: proportion of subjects with a mean 24-hour ambulatory systolic BP in the optimal range (110-129 mmHg in patients 65-79 years and 110-139 mmHg in those ≥80 years: primary outcome); additional ambulatory and home BP outcomes; A1c and lipid profile; medications, cognition, health care use, cardiovascular events, and mortality. (2) Safety outcomes: number of serious episodes of hypotension, syncope, falls, and electrolyte disturbances (requiring third party assistance or medical attention). (3) Humanistic outcomes: quality of life, satisfaction, and medication adherence. (4) Economic outcomes: incremental costs, incremental cost-utility, and cost per mmHg change in BP of telemonitoring ± case management compared with usual care (health payor and societal perspectives). (5) Intervention usability and acceptability to patients and providers.

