### Objectives

This Telemonitoring and Protocolized Case Management for Hypertensive Community-Dwelling Seniors With Diabetes (TECHNOMED) trial is designed to (1) assess the “real world” effectiveness and safety of home BP telemonitoring alone or in combination with protocolized pharmacist case management in seniors with diabetes and hypertension when compared with “enhanced” usual care; (2) evaluate the usability and acceptability of home BP telemonitoring; and (3) examine the cost-effectiveness of home BP telemonitoring alone and home BP telemonitoring plus protocolized case management.

In aggregate, these objectives will assess the impact on a comprehensive range of outcomes important to patients, providers, decision makers, industry partners, and funders.

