The 6- and 12-month follow-up data (measured as described previously) will be (1) clinical end points and patient-centered outcomes (as described previously): 24-hr ABPM, automated BP (seated, lying, and standing as described previously), telemonitored home BP, heart rate, medications, anthropomorphics, cardiovascular risk factors and markers (A1c, lipids, smoking, urinary albumin), cognition, frailty score, health care use (physician visits, emergency department visits and hospitalizations ascertained through self-report and via linked administrative health care data), quality of life and utilities, satisfaction with medical care, and depression and anxiety. (2) safety end points includes the frequency of (a) nonmechanical falls, syncope, hypotension requiring third-party assistance or medical attention and (b) electrolyte disturbances (hypokalemia [<3.3 mmol/L], hyperkalemia [>5.0 mmol/L], and hyponatremia [<130 mmol/L]. In addition, potentially life-threatening adverse effects will trigger an immediate alert causing the study team to notify the Data and Safety Monitoring Board, which will act independent of the study team to contact the patient and arrange appropriate nonstudy medical follow-up. Triggers for DSMB follow-up will include a BP ≥220/110 mmHg or a SBP <70 mmHg; potassium level ≤2.7 or ≥5.5 mmol/L; sodium level ≤126 or ≥152 mmol/L; or a PHQ-8 score ≥15, indicating severe depression. (3) User acceptability: will consist primarily of qualitative data collection. In addition, two 10-point Likert scales evaluating usability and acceptability will be collected. (4) Costing data: costing will adhere to the three-step microcosting technique of identification, measurement, and valuation of relevant health care and non–health care resources [51,52] and are outlined below and in Table 2. Resource use by category, including program start-up costs and on-going costs for each study arm, will be tabulated. In a 10% random sample of patients, time-motion studies related to the case manager will be conducted. The cost per patient will be calculated, and where any uncertainty in resource use or costs exists, plausible ranges of resource use will be determined and tested in sensitivity analysis. Resource use and cost data will be used to determine the overall and per-patient total costs, and incremental costs of interventions (telemonitoring ± case management) compared with usual care will be calculated [51,52].

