##### Data Analysis

First, variables will be examined descriptively and graphically, including assessments of temporal trends and tests of normality. Second, the 6-month and 1-year mean change from baseline in each outcome will be calculated and compared between study arms (each intervention arm to the control arm, then between intervention arms) using chi-square tests for dichotomous outcomes and unpaired *t*-tests for continuous outcomes. Third, multivariable predictors of the 1-year change in a given outcome will be identified using appropriately constructed and calibrated logistic regression models for dichotomous outcomes (including the primary outcome) or linear regression models for continuous ones. Initial models will adjust for age, sex, SBP, and residential site (eg, Greater Edmonton Foundation versus Rosedale). Examples of additional covariates that may be examined include sociodemographic variables, comorbidities, baseline medications, primary care physician, and tests of potential interaction.

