##### Methods

A validated economic model (used by the research team in prior work examining interventions in type 2 diabetes [64,65]) will be modified and used to compare both telemonitoring alone and telemonitoring + case management versus usual care (Figure 3), adhering to recommended best practices for conduct of economic evaluation [51,66]. The patient population simulated will have characteristics of the patients studied (seniors with diabetes and hypertension). The model will be informed by primary data from the RCT, including detailed costing data (Table 2), utility scores (EQ-5D), and BP changes for each treatment strategy. A 1-year time horizon and a public health care payer perspective will be used for model A, where the surrogate of change in BP will be examined (cost per mm of reduction in SBP). No discounting of costs and benefits will be performed in the reference case (given the short time frame). We will also perform a cost-utility analysis (model B) linking the validated surrogate of BP reduction at 1 year to longer term health outcomes (including probability of developing heart disease, stroke, kidney failure, blindness) [67,68], and associated increased risk of death, decrement in quality of life, and increased health care costs with these events. The model will also incorporate other study end points including avoidance of low BP and reductions in adverse effects that result in health or resource use (short-term reduction in quality of life, physician, or emergency room visits), and other health care utilization that may be impacted by treatment strategy (cost of BP drugs, clinic visits to monitor and manage BP, and hospitalizations to treat adverse effects).

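### The stated economic comparisons are all against usual care; no incremental ratio is planned for telemonitoring plus case management versus telemonitoring alone

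*Protocol article*

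**What the plan says.** The article names usual care as the economic comparator in five places:

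- Abstract, Objective: cost-effectiveness is among the properties to be examined against enhanced usual care.
- Abstract, Results: the economic outcomes include "cost per mmHg change in BP of telemonitoring ± case management compared with usual care".
- Data Collection Including End Points, costing data: "incremental costs of interventions (telemonitoring ± case management) compared with usual care will be calculated".
- Aim 3, Outcomes: "The total and incremental cost for each intervention compared to usual care will be calculated".
- Aim 3, Methods: the adapted model will be "used to compare both telemonitoring alone and telemonitoring + case management versus usual care".

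Two economic statements name no comparator. The Objectives section says the trial will "examine the cost-effectiveness of home BP telemonitoring alone and home BP telemonitoring plus protocolized case management". The uncertainty paragraph of Aim 3, Methods plans acceptability curves over a range of willingness-to-pay thresholds without saying which strategies enter them.

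The clinical plan does make the missing contrast. Data Analysis sets the order of comparisons as "each intervention arm to the control arm, then between intervention arms", and Sample Size Considerations claims power for a "similar 20% difference between the 2 intervention arms".

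**The concern.** The third arm is the second arm plus a pharmacist case manager. A payer who could have telemonitoring alone needs to know what the case manager adds and at what cost. The Summary of Rationale treats this as an open question: it sets out patient-reported home readings, automated telemonitoring, and telemonitoring with case management as three candidate methods, and says that the best choice is unsettled on costs as well as effectiveness.

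A ratio against usual care does not answer that question, because it pools the gain that telemonitoring already delivers with the gain from the added step. Followed as written, the plan could report an acceptable ratio for case management when the added step is inefficient, or when telemonitoring alone is no less effective and cheaper.

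**Working it through.** The document gives no cost, cost per mmHg or cost per QALY, so there is no stated figure to reproduce. The check is on the algebra and on what the sections say.

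**Notation.** C1 and E1 are the added cost and effect of telemonitoring (TM) over usual care (UC). c and e are the further cost and effect of case management (CM) over TM.

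**Identity.** With E1 > 0 and e > 0:

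CM vs UC = (C1 + c)/(E1 + e) = [E1/(E1 + e)] × (C1/E1) + [e/(E1 + e)] × (c/e)

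This is an average of TM vs UC (C1/E1) and CM vs TM (c/e), weighted by effect. It therefore lies below c/e exactly when c/e > C1/E1, equals c/e when the two ratios are the same, and lies above c/e when c/e < C1/E1.

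**Illustration in the unit of model A.** All inputs are assumptions: C1 = 300 and E1 = 5 mmHg, so TM vs UC = 300/5 = 60 per mmHg throughout.

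| c | e (mmHg) | CM vs UC | CM vs TM | Usual-care ratio as a guide to the added step |
|---|---|---|---|---|
| 600 | 2.5 | 900/7.5 = 120 | 600/2.5 = 240 | understates (half) |
| 300 | 1 | 600/6 = 100 | 300/1 = 300 | understates (one third) |
| 300 | 5 | 600/10 = 60 | 300/5 = 60 | equal |
| 100 | 2.5 | 400/7.5 = 53.3 | 100/2.5 = 40 | overstates (by a third) |
| 300 | 0 | 600/5 = 120 | no gain for 300 | CM is dominated by TM |

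Check of the identity on the first row: (5/7.5) × 60 + (2.5/7.5) × 240 = 40 + 80 = 120.

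The first and last rows give the same figure against usual care, 120 per mmHg. In one the added step costs 240 per mmHg; in the other it buys nothing. The CM vs UC ratio cannot tell them apart.

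Over c from 100 to 900 and e from 1 to 5, CM vs UC runs from 40 to 200 while CM vs TM runs from 20 to 900.

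**The fourth row.** There CM vs TM (40) is below TM vs UC (60), so TM alone is extendedly dominated and drops out of the ordering. CM vs UC (53.3) is then the correct sequential ratio. The planned comparison is thus sufficient in some configurations, but only a sequential analysis shows which one applies.

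**Data needed.** Data Collection Including End Points tabulates resource use and cost for every arm and includes time-motion work on the case manager. Aim 3, Methods feeds BP change by strategy and EQ-5D utilities into the model. C1, c, E1 and e can therefore all be estimated from planned data.

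**The case against.** Several points on the other side are fair.

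- A reader might infer that case management is never costed apart from telemonitoring. The document does not support this: costs are tabulated by arm and cost per patient is calculated. What is absent is a planned incremental comparison of the two intervention arms. If incremental costs and effects are both reported against usual care, a point estimate of that comparison can be obtained by subtraction. Its uncertainty cannot be read off the two separate contrasts, because they share the usual-care arm.
- A reader might also infer that every economic statement restricts the comparison to usual care. It does not: the Objectives section and the acceptability-curve sentence name no comparator, and nowhere does the text say that usual care is the sole one.
- Usual care is a legitimate baseline. The Introduction says these interventions are not in use in Canada, so a payer will want each of them against current practice. The usual-care ratio answers that question correctly.
- This is a condensed article. The model overview (Figure 3) is not shown, and Aim 3, Methods commits to accepted good practice in economic evaluation. A fuller economic plan might order the strategies.

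The last point would carry the day if the article were silent on the comparator. It is not: the sentences that cite Figure 3 and good practice are the ones that name usual care. That is a stated method, repeated in several sections, rather than detail left for elsewhere.

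**Conclusion.** The point stands as a gap in the stated economic comparisons, and it should be corrected. For three mutually exclusive strategies, two ratios against a common baseline do not by themselves show whether the added step is worth its cost.

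The direction is conditional. It would be tempting to say that the planned figure makes case management look too cheap. That holds only if CM vs TM exceeds TM vs UC, or if case management adds cost without benefit. At equal ratios there is no discrepancy, and beyond that it reverses. If telemonitoring both saves money, as the Summary of Rationale hopes, and adds benefit, it dominates usual care, and usual care is then not the relevant comparator for case management.

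No size can be given. A reader might try to derive one from the assumed gains of 20 and 40 percentage points over usual care in Sample Size Considerations, with the case-management arm costing k times as much extra as telemonitoring. The ratios are then k/2 and k − 1 in common units. That gives an understatement of 25% at k = 3 (1.5 vs 2), none at k = 2 (1 vs 1), and an overstatement of 50% at k = 1.5 (0.75 vs 0.5). The document supports no value of k, and the proportion in range is the unit of neither planned model: model A uses SBP and model B uses QALYs.

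The conclusion rests on the identity above and on the article's text; Figure 3 and any fuller economic plan were not available.

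**What to change.** In Data Collection Including End Points (costing data) and in Aim 3, Outcomes and Methods, state that:

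1. The three strategies will be ordered by cost, and dominated and extendedly dominated ones removed.
2. Sequential incremental ratios will be reported for models A and B. The incremental cost and effect of case management versus telemonitoring alone will be shown in every case, including where one of the two is dominated.
3. All three strategies will enter the probabilistic analysis and the acceptability curves together.
4. The ratios of each intervention against usual care will be kept as secondary results.

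The cost is a few sentences. The change uses costs, BP changes and utilities already collected by arm, needs no further patients or visits, and brings the economic aim into line with the between-intervention comparison in the clinical analysis.
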